### Secondary outcome measures

*Strengths and Difficulties Questionnaire (SDQ):* Described previously. It will be completed by the young people, parents and teachers at baseline and post-intervention.

*Social Responsiveness Scale (SRS):* Described previously. It will be completed online by parents and teachers at baseline and post-intervention.

*Spence Social Worries Scale (SWS):* The Spence Social Worries Scale is a psychological questionnaire designed to identify symptoms of social phobia and other forms of anxiety, in children and adolescents. The parent and teacher forms are reported to have excellent internal validity
^35^. It will be completed online by the adolescents, parents and teachers at baseline and post-intervention.

*Schedules for the Assessment of Social Intelligence (SASI):* Described previously. It will be administered online to the adolescent at baseline and post-intervention.

*PEERS Test of Adolescent Social Skills Knowledge (TASSK):* The TASSK is a questionnaire designed to evaluate what the participants have learned from the intervention
^18^. This is the only outcome measure to evaluate changes in social knowledge. It will be administered to the adolescents at baseline and post-intervention.

*PEERS Quality of Socialisation Questionnaire (QSQ):* The QSQ is designed to evaluate the quality of young people’s socialization and frequency of get-togethers
^18^. It will completed online by the parents at baseline and post-intervention.

*Rosenberg Self-esteem Scale (RSE):* The RSE scale is assesses global self-esteem
^36^. It will completed online by the adolescent at baseline and post-intervention.

*Beck’s Anxiety Inventory (BAI):* This scale is a self-report measure used for measuring the severity of anxiety in children and adults
^37^. It will be completed online by the parent and adolescent groups at baseline and post-intervention.

*Camouflaging measure (CAT-Q):* The CAT-Q measures camouflaging (e.g. strategies to mask or compensate autistic characteristics) behaviour in social situations. It is comprised of 25 items and has high internal reliability in autistic adults. Its subscales measure compensation, masking and assimilation
^38^. The CAT-Q will be completed by adolescents.

*Intervention Acceptability Questionnaire (IAQ):* The IAQ has been developed for the study to assess parent and adolescent satisfaction with the intervention (
Supplementary File 1). It will be completed by the parent and adolescent groups once the intervention has ended.

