### Assessments

Participants will complete assessments at different time points throughout the study. The study will last 9 months in total, including a 3 month baseline, 2 months of intervention and a 3 month follow-up period. The screening measures will be delivered at T=0, the baseline assessments will be delivered at T=12 weeks and the post intervention assessments will be delivered at T=20 weeks. The primary outcome measure will be delivered at regular intervals of 4 weeks throughout the course of the study (see
Table 1).

**Table 1. T1:** Assessment timeline. Informants for each assessment are included in brackets (P – Parent; T – Teacher; YP – Young Person). Assessment acronyms: BAI – Beck’s Anxiety Inventory; IAQ – Intervention Acceptability Questionnaire; PEERS – Program for Education and Enrichment of Relational Skills; PEERS QSQ – PEERS Quality of Socialisation Questionnaire; PEERS TASSK – PEERS Test of Adolescent Social Skills Knowledge; RSE – Rosenberg Self-esteem Scale; SCP – Social Competence with Peers; SDQ – Strengths and Difficulties Questionnaire; SRS – Social Responsiveness Scale; SASI - Schedules for the Assessment of Social Intelligence; SWS – Spence Social Worries Scale; WAIS-Wechsler Adult Intelligence Scale.

Timeline	Assessments
t=0	SCP (P) 1 PEERS Screener (P,YP) SASI (YP) WAIS (YP)
4 weeks	SCP (P) 2
8 weeks	SCP (P) 3
**Baseline** 12 weeks	SCP (P,YP,T) 4 SWS (P,YP,T) PEERS QSQ (P) PEERS TASSK (YP) RSE (YP) BAI (YP) SRS (P,T) SDQ (P,T)
16 weeks	SCP (P) 5
**Post-intervention** 20 weeks	SCP (P) 6 SWS (P,YP,T) PEERS QSQ (P) PEERS TASSK (YP) RSE (YP) BAI (YP) SRS (P,T) SDQ (P,YP,T) IAQ (P,YP) SASI (YP)
24 weeks	SCP (P) 7
28 weeks	SCP (P) 8
**Follow-up** 32 weeks	SCP (P,YP,T) 9

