### Screening assessments

*Development and Wellbeing Assessment (DAWBA):* The
DAWBA will be used to collect information on the child’s behavioural adjustment and mental health. The DAWBA has been used both in UK national and international surveys
^25–
28^. The DAWBA data will be reviewed by a psychiatrist in accordance with the ICD-10/DSM-V diagnostic criteria. This methodology has been used successfully to gather data of high quality by parental online report. The DAWBA autism module includes a social aptitude scale (SAS) which measures social understanding and social ability (Liddle
*et al*., 2009). Participants displaying significant difficulties in the SAS will be eligible for the intervention. The DAWBA is available in 26 languages. The DAWBA will be completed online by parents.

*Strengths and Difficulties Questionnaire (SDQ):* The
SDQ is a brief behavioural screening questionnaire
^29^. The SDQ includes scales that measure emotional symptoms, conduct problems, hyperactivity/inattention difficulties, peer relationship problems and prosocial behaviour. The first four scales are combined to create a total difficulties score. An additional impact scale measures the impact of this composite score on daily life. Participants scoring poorly on the peer relationships subscale will be eligible for the intervention. It has been validated for use in children aged 4–17 in UK National studies of psychological adjustment, and a new form for 18+ years old has recently been developed. It will be completed online by the adolescents, parents and teachers.

*Social Responsiveness Scale (SRS):* The SRS measures the severity of autistic traits and the instrument has convergent validity with other ASD diagnostic tools
^30,
31^. The SRS subscales measure Social Awareness, Social Cognition, Social Communication, Social Motivation, and Restricted Interests and Repetitive Behaviour. The SRS will be administered online to parents and teachers.

*Health Questionnaire (HQ):* The questionnaire was developed by the UCLH Turner Syndrome Life Course Project to record information about physical health, health care, education, social life, physical activity and relationships
^32^. The self-report version of the questionnaire will be completed by adolescents. 

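### Table 1 schedules no adolescent SDQ at the week-12 baseline and takes the SASI at week 0, contrary to the Secondary outcome measures section

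*Protocol article*

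**What the plan says.** The Assessments section (Protocol article) fixes the time points: "The screening measures will be delivered at T=0, the baseline assessments will be delivered at T=12 weeks". Post-intervention assessments follow at week 20, and Table 1 labels its week-12 row as baseline.

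The Secondary outcome measures section then assigns informants and times:

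- SDQ: "It will be completed by the young people, parents and teachers at baseline and post-intervention".
- SASI: "It will be administered online to the adolescent at baseline and post-intervention".
- BAI: "It will be completed online by the parent and adolescent groups at baseline and post-intervention".

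Table 1 gives a different schedule:

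- Week 0: "SCP (P) 1 PEERS Screener (P,YP) SASI (YP) WAIS (YP". The SASI is listed and the SDQ is not.
- Week 12: "RSE (YP) BAI (YP) SRS (P,T) SDQ (P,T". The young person is not an SDQ informant, the BAI is self-report only, and the row contains no SASI.
- Week 20: "SRS (P,T) SDQ (P,YP,T) IAQ (P,YP) SASI (YP". The young person is now an SDQ informant, and the SASI appears.

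The Statistical analysis section plans pre-post comparisons of the secondary outcomes with Cohen's d. It predicts that adolescents will gain more on the TASSK than on the SCP or SDQ (prosocial or peer scale) and the SASI. It also predicts that adolescents will report larger gains than the other informants.

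**The concern.** The text and Table 1 cannot both be carried out. Staff who work from Table 1 will collect an adolescent SDQ after treatment with no week-12 score to set against it. They will also hold a SASI pre-score taken 12 weeks before treatment starts.

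Two named comparisons depend on these scores. One sets adolescent SDQ and SASI gains against the TASSK gain. The other sets adolescent SDQ change against parent and teacher change. The trial has no control group, and neither measure has the repeated pre-treatment series that the parent SCP has. Nothing else in the design would therefore separate untreated change from change during treatment. A week-12 score that is not collected cannot be recovered later.

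**Working it through.** No figure in the plan needs reproducing. The check compares the text with the table and counts weeks.

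**Inputs.** Screening is at week 0, baseline at week 12 and post-intervention at week 20 (Assessments). The intervention lasts 2 months after a 3-month baseline, so it fills weeks 12 to 20. This assumes that treatment starts directly after the week-12 assessment.

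**Adolescent measures, text against table**

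| Measure | Text: pre / post | Table 1: pre / post |
|---|---|---|
| SDQ | week 12 / week 20 | none / week 20 |
| SASI | week 12 / week 20 | week 0 / week 20 |
| TASSK | week 12 / week 20 | week 12 / week 20 |

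**Interval = post week minus pre week**

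- TASSK: 20 − 12 = 8 weeks, all within the treatment window.
- SASI under Table 1: 20 − 0 = 20 weeks. The untreated part is 12 − 0 = 12 weeks, and 12/20 = 60%.
- SASI under the text: 20 − 12 = 8 weeks.
- Adolescent SDQ under Table 1: one time point, so there is no change score.
- Adolescent SDQ with the screening score substituted: 20 − 0 = 20 weeks, again with 12 untreated. The parent and teacher SDQ would cover 20 − 12 = 8 weeks.

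**Status of the screening SDQ.** The Screening assessments section has adolescents complete the SDQ, so an earlier score may exist although Table 1 does not show it at week 0. The same section uses the instrument for selection: "Participants scoring poorly on the peer relationships subscale will be eligible for the intervention". A pre-score that helped to select participants tends to move back toward the average on retest, so some regression to the mean on the peer scale is possible. The documents do not supply what is needed to size it: the cut-off, the retest correlation, or whose SDQ decides eligibility.

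**BAI.** The text names parents and adolescents. Table 1 names adolescents only, at both week 12 and week 20.

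**The case against.** The strongest reply is that this is a slip in a table. The text plans the young person's SDQ at baseline, and Table 1 includes the young person at week 20, so a dropped informant code at week 12 is at least as likely as a deliberate plan with no pre-score. That is fair. It makes this a contradiction to reconcile, and it does not show that the investigators intend to omit the measure.

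On the SASI, the instrument is also listed under Screening assessments, which fits week 0, and the Assessments section calls the first three months a baseline period. A loose reading of baseline could therefore include week 0. But the same section and the table label both place the baseline assessment at week 12. Even on the loose reading, the SASI and TASSK intervals remain 20 and 8 weeks.

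A reader might go further and infer that selection on the SDQ would by itself produce an apparent gain as large as a medium treatment effect. For example, if participants were the worst 20% on the peer scale (mean 1.40 SD from the average), a retest correlation of 0.6 to 0.8 would give (1 − r) × 1.40 = 0.56 to 0.28 SD. The documents do not support using that figure:

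- They do not say that the screening score will be the pre-score.
- They do not say that the adolescent's own rating drives selection, and they give no 20% cut-off.
- The social aptitude scale, clinical judgement and motivation also enter selection.
- The prosocial scale is not named as a criterion.
- Only the upper end of the range would count as medium.

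Direction matters too. Regression, practice or untreated improvement would enlarge the SDQ and SASI gains, which works against the prediction that the TASSK gain is larger. Such change would flatter the intervention only in the SDQ and SASI effect sizes themselves, or in the comparison of adolescents with other informants.

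Finally, these are secondary outcomes in an uncontrolled pilot of 6–10 participants that the plan itself expects to be underpowered. The parent SCP series and the acceptability aim are untouched.

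**Conclusion.** The schedule is wrong as written, because the text and Table 1 contradict each other on three secondary measures. If Table 1 is followed, the adolescent SDQ pre-post change and its Cohen's d cannot be computed from the scheduled assessments. The only substitute is a screening score dated 12 weeks before treatment, with possible regression to the mean of unknown size on the peer scale. The SASI change remains computable, but 12 of its 20 weeks are untreated and it does not match the 8-week TASSK interval.

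These findings need only the document's own dates and the assumption that treatment starts just after week 12. The documents contain no evidence that SASI scores drift without treatment, so the interval mismatch is a problem of interpretation and not a demonstrated bias. The point should be settled before the week-12 assessments. It does not affect the primary outcome.

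**What to change.** - **SDQ.** Change the week-12 entry in Table 1 to SDQ (P,YP,T), and state that the SDQ pre-score is the week-12 score and not the screening score. The cost is one short questionnaire per participant, which the text already promises.
- **SASI.** Reconcile the text with Table 1 in one of two ways. Either give it at week 12 as the text says, which costs one more online session and one more practice exposure if the week-0 SASI is kept. Or keep week 0 as the pre-score and say plainly that the change includes 12 untreated weeks and is not matched in time to the TASSK. The second option costs only a sentence.
- **BAI.** State whether parents complete it, and make the text and table agree.

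A blanket rule that every secondary outcome uses a week-12 pre-score would not work, because the IAQ is given only after the intervention and the CAT-Q does not appear in Table 1. Nor do these changes restore the whole adolescent prediction. Table 1 takes the week-20 SCP from parents only, so the adolescent SCP part needs its own correction.

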### Study design

We will be employing an uncontrolled trial design. To maximise the clinical reliability of the trial we will use a systematic multiple-case series design with case tracking. We aim to recruit participants with a similar degree of social impairment, and intellectual ability.

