### Sample size

A sample size of 6–10 girls and their parents will be invited to take part in the study - this is the group size recommended by the PEERS intervention manual. At present the effect size for this intervention in girls with TS is unknown. This pilot will serve as the basis to estimate the intervention’s effect size and sample size for a future randomised control trial.

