*Schedules for the Assessment of Social Intelligence (SASI):* The SASI is a socio-cognitive assessment that measures facial expression recognition, face recognition memory, gaze-monitoring and theory of mind. The SASI is sensitive to subtle deficits in social cognition and has been shown to have excellent reliability and validity
^33^. Adolescents will be asked to complete the SASI online.

*Wechsler Adult Intelligence Scale - Fourth UK Edition (WAIS-IV UK):* The WAIS-IV is an IQ test which measures verbal comprehension, perceptual reasoning, working memory and processing speed. It has been widely used and validated
^34^. It will be administered to adolescents in person.

*PEERS Screener:* The PEERS Screener Questionnaire assesses the participant’s motivation to take part in the PEERS intervention
^18^. It will be administered to parents and adolescents over the phone or in person. Only participants motivated to take part will be considered for the intervention.

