### Statistical analysis

The primary outcome measure (SCP questionnaire)
^16^ will be analysed using visual analysis and multi-level modelling to track individual participant changes over 9 months from baseline to follow up
^39^.

The secondary outcome measures will be analysed for pre-post differences. Data will be analysed using SPSS version 22 statistical software. It is likely that we will be underpowered to detect any significant statistical differences between the pre and post intervention scores; therefore effect sizes (Cohen’s d) will also be calculated. The parent, teacher and adolescent responses to the questionnaires will also be compared to investigate the consistencies between different informants.

We anticipate that adolescent informants will report the greatest positive changes compared to other informants. We also anticipate that the adolescents will report greater improvements on the social knowledge on the TASSK, than on the social performance on the SCP or SDQ (prosocial or peer scale) and social cognition on the SASI. We also expect to see secondary improvements on adolescent self-reports of anxiety on the BAI raw score, social anxiety on the SWS raw total score and self-esteem on the RSE raw total score. We expect to see an increase in camouflaging on the CAT-Q on all the subscales.

In line with previous social skills intervention research we anticipate that positive changes in social performance will be noted by the parents, but that schoolteachers will not observe a change post intervention on the SRS, SDQ and SWS. Specifically we expect parents to report improvements in the SWS total raw score, as well as improvements on the SDQ raw prosocial scale and peer difficulties scale, and improvements on the SRS social communication scale and repetitive and ritualised behaviours scale.

The acceptability of the intervention to families will be assessed using the IAQ. Descriptive statistics will be used to summarise the responses alongside a qualitative summary of the open text answers. We expect that most families will report having positive experiences of the PEERS programme. Based on previous randomised controlled trials we predict that adherence will be on average 80% and that up to two participating families may dropout (Laugeson
*et al.,* 2015; Schohl
*et al.,* 2014).

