The assessment battery has been designed to measure changes in social skills, in the domains of social performance, social knowledge and social cognition. These outcomes will be reported on by the parents, teachers and the young people themselves. Teachers and parents will be asked to report on changes in social performance through questionnaires. The young people will complete questionnaires which measure social performance and social knowledge, as well as an online task to measure changes in social cognition. The maintenance of any potential treatment gains in social performance will be assessed by the parent report at a 3 month follow-up.

It is likely that the adolescent and parent reports will be prone to expectancy biases
^43^. They may exaggerate treatment effects due to their investment in taking part in the intervention. Using external observers (such as teachers or blinded study administrative assessors) is essential to help understand these biases and assess whether changes in performance generalise to other settings
^41,
44^. Unfortunately, due to the small scale of this project, assessments by external observers will not be feasible.

Meta-analyses of social skills interventions for children on the autistic spectrum using the SRS have shown that the largest treatment gains are made in the social communication and repetitive and ritualised behaviours scale
^21^. The changes in repetitive and ritualised behaviours may be mediated by reductions in anxiety or increases in social awareness
^21,
45^. The majority of the participants included in the meta-analyses were adolescent males, therefore it remains to be seen whether these patterns of improvement will be replicated in females with TS.

This study will also use a novel measure of social camouflaging
^46^. Social camouflaging is a strategy adopted by people on the spectrum to manage social situations. It has been likened to wearing a ‘social mask’, where the individual puts on ‘their best self’
^46^. Camouflaging typically involves masking and compensating for social deficits
^46–
48^. This might involve consciously performing a range of non-verbal cues such as making eye contact during conversations and imitating facial expressions and gestures, or following learnt social scripts such as using pre-prepared jokes or comments
^49^. Recent research suggests that females are better at camouflaging than males
^48,

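### As tabled, the SASI pre-post effect size cannot separate a treatment effect from retest gain and 12 untreated weeks; adding the week-12 sitting that the text implies would help

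*Protocol article*

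**What the plan says.** All references are to the protocol article.

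- **Nature of the test.** Screening assessments describes the SASI as an assessment that "measures facial expression recognition, face recognition memory, gaze-monitoring and theory of mind". The Discussion contrasts it with the questionnaires the young people complete, "as well as an online task to measure changes in social cognition". It is therefore a scored task, not a rating.
- **Timing in the text.** The SASI is described under Screening assessments, and the Assessments section places screening measures at T=0. Secondary outcome measures then says: "It will be administered online to the adolescent at baseline and post-intervention". The Assessments section sets baseline at T=12 weeks and post-intervention at T=20 weeks.
- **Timing in Table 1.** The SASI appears at t=0 and at week 20. It is absent from the week-12 row, which is the one labelled Baseline.
- **Design and analysis.** Study design states: "We will be employing an uncontrolled trial design". Statistical analysis states: "The secondary outcome measures will be analysed for pre-post differences", and adds Cohen's d.
- **Use of the result.** Objectives and hypothesis says that training may improve social cognition. Statistical analysis predicts that gains on the TASSK will exceed those on the SASI.

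**The concern.** A second sitting of a recognition, memory and theory-of-mind task can score higher because the task and stimuli are familiar. With no control group and a single sitting before treatment, the planned data cannot show how much of a change is of that kind. On Table 1's timing, the change also takes in 12 weeks before the intervention starts.

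What is at stake is the reading of one secondary outcome that carries a stated hypothesis. The Discussion warns about expectancy bias in parent and adolescent reports but does not mention practice. Because the SASI is not a report, a reader could take it as the cleaner evidence. An analysis plan written later cannot recover an untreated retest that was never collected, so this has to be settled in the schedule.

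**Working it through.** The plan gives no SASI effect size, retest figure or power to reproduce. The check compares the schedules first and then illustrates the size.

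**1. Sittings by source**

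| Source | t=0 | Week 12 | Week 20 |
|---|---|---|---|
| Table 1 | yes | no | yes |
| Secondary outcome measures, read with Assessments | not stated | yes | yes |
| Screening assessments, read with Assessments | yes | not stated | not stated |

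The two text sections together are compatible with three sittings; Table 1 shows two. The sources need reconciling.

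**2. What each schedule measures**

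Let T be the treatment effect, G the retest gain and D the change over time without treatment.

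- Table 1 (0 to 20): expected change = T + G + D over 20 weeks. Of these, 12/20 = 60% precede the intervention.
- Weeks 12 and 20 only: T + G + D over 8 weeks. The lead-in drops out; the retest gain does not.
- Three sittings: 0 to 12 gives G1 + D12, and 12 to 20 gives T + G2 + D8. The difference is T + (G2 − G1) + (D8 − D12). It equals T only if practice and drift are equal in the two intervals.

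**3. Illustration of size with T = 0 and D = 0**

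Assumed, because the documents give no values: retest gain g = 0.2 to 0.5 SD and retest correlation r = 0.6 to 0.8. From the plan: n = 6 to 10.

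- Cohen's d on the baseline SD equals g, so 0.2 to 0.5.
- Cohen's d on the SD of change equals g/√(2(1−r)). The lowest value is 0.2/√0.8 = 0.22 and the highest is 0.5/√0.4 = 0.79. The plan does not say which standardiser it will use.
- The chance of a significant improvement (paired t, two-sided 0.05, non-centrality d√n with d on the SD of change) is 6.6% to 34.9% at n=6 and 9.3% to 60.6% at n=10. The nominal chance in that direction is 2.5%.

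**4. Precision of the comparison with three sittings**

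- 95% half-width of one mean change, t(n−1)·√(2(1−r)/n), in SD units: at n=6, 0.94 (r=0.6) and 0.66 (r=0.8); at n=10, 0.64 and 0.45.
- The difference of the two changes is Y20 − 2·Y12 + Y0. With equal variances and equal correlations its variance is 6(1−r). The half-width is t(n−1)·√(6(1−r)/n). At n=6, r=0.6 this is 2.571·√(2.4/6) = 1.63. At n=10, r=0.8 it is 2.262·√(1.2/10) = 0.78.

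The half-width of about 0.8 to 1.6 SD exceeds the whole assumed gain of 0.2 to 0.5 SD. The untreated change can therefore inform interpretation but cannot serve as a formal correction.

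**The case against.** The strongest reply is that every single-arm pre-post change mixes treatment with time and retesting. The authors declare the design, expect to be underpowered and defer efficacy to a later randomised trial. That stands as a limit on weight. It does not make the point empty, because the protocol already repeats the SCP four times up to week 12 and the SASI has no comparable lead-in.

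Several stronger readings are tempting, and the documents do not support them:

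- *The plan fixes exactly two sittings.* Only Table 1 does; the text is compatible with three.
- *Practice will produce the SASI gain.* No retest data are given, the gain is assumed, and a gap of 20 weeks may shrink it.
- *No alternate form exists.* The article does not mention one, but silence in a condensed article proves nothing.
- *The planned ordering of gains would be distorted in the authors' favour.* The prediction is that the TASSK gain exceeds the SASI gain, so SASI practice taken alone works against it. The TASSK is also a test given twice, so the net direction is unknown.
- *The future trial would be missized.* Sample size says "This pilot will serve as the basis to estimate the intervention’s effect size and sample size for a future randomised control trial", but nothing says that the SASI effect size will be used.

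It is also fair to object that requiring the treated change to exceed the untreated one would be a poor rule. Apart from the imprecision, the intervals differ (12 versus 8 weeks), and practice may be larger at the first retest, so a real gain could be hidden.

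**Conclusion.** The point holds in a limited form. Table 1 and Secondary outcome measures disagree on when the first SASI outcome sitting falls. As tabled, the SASI effect size cannot separate treatment from retest gain and 12 untreated weeks. This follows from the schedule and the uncontrolled design and needs no assumption.

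The size is not known. Under the assumed gain of 0.2 to 0.5 SD and correlation of 0.6 to 0.8, d would be 0.2 to 0.5 on the baseline SD, or 0.22 to 0.79 on the SD of change, with no treatment effect at all. The range shows that the artefact could matter, not that it will occur.

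The reach is one secondary outcome. The SCP has repeated pre-treatment measurements and is not touched. The change is worth making because it is specific and cheap, not because the pilot's main aims depend on it.

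**What to change.** 1. Reconcile Assessments (with Table 1), Screening assessments and Secondary outcome measures: keep the SASI at t=0 and add it to the week-12 row of Table 1.
2. Define the SASI pre-post difference as the change from week 12 to week 20.
3. Report each girl's untreated change from t=0 to week 12 beside it, descriptively. This suits the case-series design. Do not use it as a threshold.
4. Name practice as a limitation, and say whether alternate forms are used.
5. If only two sittings are kept, state that SASI change cannot be separated from practice and make no improvement claim from it.

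The cost is one extra online sitting per girl, 6 to 10 in all, within a week-12 battery that already exists, plus one descriptive summary. The downside is a little more participant burden and one more exposure to the task before treatment.

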## Protocol

### Objectives and hypothesis

The main objectives of the study are:

1) To pilot the PEERS intervention in adolescents with TS;2) Assess its feasibility and acceptability to families.

We hypothesise social skills training will improve social competence with peers and may produce secondary improvements in social cognition, self-esteem and anxiety (social and generalised).

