### Participant inclusion and exclusion criteria

Inclusion criteria for the intervention include: 1, a confirmed diagnosis of TS (monosomy, variant, mosaic etc.); 2, age 16–20 years; 3, significant social skills difficulties as screened for in the SOAR online questionnaires (see screening assessment measures section for details) and clinical judgement; 4, motivation to take part.

The exclusion criteria for the intervention include: 1, profound hearing or vision impairments (eg. complete deafness or blindness); 2, intellectual disability (VIQ<70); 3, concurrent participation in other psychological treatment.

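### Acceptability, part of a main objective, is measured once after the programme ends, with no scheduled point for families who leave early to give their view

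*Protocol article*

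**What the plan says.** All references are to the protocol article.

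- **Objective.** The second main objective in Objectives and hypothesis is: "Assess its feasibility and acceptability to families".
- **Instrument.** Statistical analysis names one: "The acceptability of the intervention to families will be assessed using the IAQ". The responses are to be summarised descriptively, with a qualitative summary of the free-text answers.
- **Timing.** Secondary outcome measures says of the IAQ: "It will be completed by the parent and adolescent groups once the intervention has ended". Table 1 (Assessments) agrees. The IAQ, for parent and young person, stands only in the post-intervention row at week 20.
- **Expected result.** Statistical analysis states: "We expect that most families will report having positive experiences of the PEERS programme". No numerical threshold is attached.
- **Expected loss.** The same section forecasts average adherence of 80% and that "up to two participating families may dropout".
- **Group size.** Sample size gives: "A sample size of 6–10 girls and their parents will be invited to take part in the study".
- **Handling of loss.** Missing data and intervention adherence provides for reporting missing data by questionnaire and time point, and for reporting adherence, planned absences and dropouts. Causes are given where they can be obtained.
- **Eligibility.** "motivation to take part" is an inclusion criterion. Under the PEERS Screener, Screening assessments adds: "Only participants motivated to take part will be considered for the intervention".

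**The concern.** A family may leave because the programme, or its mix of online and face-to-face delivery, does not suit it. If so, dropout is itself related to acceptability, and missing IAQ responses from leavers would be informative. The plan forecasts such losses, yet its only IAQ slot comes after the programme has finished. The intervention lies between the week 12 baseline and the week 20 assessment, so a family that leaves early has no scheduled assessment of its view. Even if it were contacted at week 20, it could be answering up to about 20 − 12 = 8 weeks after leaving.

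Two uses of the result are affected. The Abstract says that feedback will be used to adapt the programme, and the Discussion says that it will inform later replications. The families best placed to say what should change may be those not heard. The Discussion also accepts that parents and young people may overstate benefit because they are invested in the programme. Losing the least invested families would push in the same direction.

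**Working it through.** The plan gives no acceptability proportion, precision or threshold, so there is no figure to reproduce. The check is a bounding calculation on the plan's own numbers.

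**Inputs**
- *n*, families who start: 6 to 10 (Sample size). The text speaks of families invited; I take all of them to start.
- *d*, families who drop out: up to 2 (Statistical analysis), so 1 or 2.
- *k*, completing families with a positive view: free to vary from 0 to *n − d*.
- Assumptions: the family is the unit, and a majority means more than 50%. The protocol fixes neither.

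**Formulas**, if leavers give no IAQ
- Share of families with no response: *d/n*.
- Share positive among completers: *k/(n − d)*.
- Share positive among starters: at worst *k/n* (no leaver positive), at best *(k + d)/n* (every leaver positive).
- Overstatement in the worst case: *k/(n − d) − k/n*. This is largest when every completer is positive (*k = n − d*), where it equals *d/n*.

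**Two dropouts**

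| *n* | No response | All completers positive: worst case among starters | Case where the majority is lost (completers vs worst case) |
|---|---|---|---|
| 6 | 2/6 = 33% | 4/6 = 67% | 3/4 = 75% vs 3/6 = 50% |
| 7 | 2/7 = 29% | 5/7 = 71% | 3/5 = 60% vs 3/7 = 43% |
| 8 | 2/8 = 25% | 6/8 = 75% | 4/6 = 67% vs 4/8 = 50% |
| 9 | 2/9 = 22% | 7/9 = 78% | 4/7 = 57% vs 4/9 = 44% |
| 10 | 2/10 = 20% | 8/10 = 80% | 5/8 = 63% vs 5/10 = 50% |

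At every group size there is at least one result that reads as a majority among completers but not, in the worst case, among starters. The maximum overstatement is 33 percentage points at *n* = 6 and 20 at *n* = 10.

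**One dropout.** The share with no response is 1/6 = 17% to 1/10 = 10%. The majority can be lost only at *n* = 6 (3/5 = 60% vs 3/6 = 50%), *n* = 8 (4/7 = 57% vs 4/8 = 50%) and *n* = 10 (5/9 = 56% vs 5/10 = 50%).

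**The other bound.** With *n* = 6, *d* = 2 and *k* = 3, the share among starters lies between 3/6 = 50% and (3 + 2)/6 = 83%, around a completer figure of 75%. The completer figure can therefore be wrong in either direction. The upward direction is the likelier one if dissatisfaction contributes to leaving, but the documents give no figure for that.

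**The case against.** The strongest reply is that the text contains no completers-only rule. It assigns the IAQ to the parent and adolescent groups and does not say that families who leave are not asked. Adherence and study dropout are listed separately, so a family that stops attending could remain in the study and receive the week 20 form. A condensed article may also leave withdrawal procedures to a fuller document. This stands in part. A reader might infer that dropouts never answer, but the documents do not say so. What the article does state is the timing, and neither the IAQ description nor Table 1 has a slot at withdrawal.

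Second, the loss would not be hidden. Missing IAQs, dropouts and, where possible, reasons are to be reported, and the forecasts for adherence and dropout stand in the same paragraph as the IAQ analysis. This also stands: in a group this small a reader would see how many families did not respond. But a count of missing forms does not say what those families thought, and a recorded reason for leaving is not an acceptability response.

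Third, the plan defines no headline proportion and no decision rule, and leavers may go for reasons unrelated to the programme. So the percentages above are bounds on a summary that the protocol does not itself specify. Counting silent leavers as not positive is a contestable imputation. Both points are right and limit what can be claimed.

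Fourth, a reader might infer that the motivation screen selects respondents a second time and so biases the result. The documents do not support that. Motivation is a declared eligibility criterion and helps to define the population studied. It limits generalisation to less motivated families but does not in itself distort acceptability among eligible ones.

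**Conclusion.** The point holds as a risk of upward bias on part of a main objective, not as a demonstrated bias. The stated schedule measures acceptability after the programme has ended, while the plan forecasts losing up to 20% to 33% of families. It provides no point at which those families' views enter the result.

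In the worst case with two dropouts, a unanimous result among completers corresponds to 67% to 80% of starters. This rests on leavers not answering and all of them being counted as not positive. If leavers answer, or share the completers' views, the bias is zero.

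A reader might go further and conclude that the result is biased, or that a favourable finding is almost assured. Neither follows: the views of leavers are unknown, and completers may rate the programme poorly. The trial remains sound. This is an inexpensive improvement to stated data collection.

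**What to change.** 1. In Secondary outcome measures and Table 1, offer the IAQ to parent and young person at withdrawal or at week 20, whichever comes first.
2. In Statistical analysis, report IAQ responses with all families who started the programme as the denominator, beside the result among completers.
3. Show leavers who do not respond as a separate count, next to the dropout and adherence figures already planned. Use the not-positive assumption only as a labelled sensitivity bound.
4. State that the finding applies to families who met the motivation criterion.

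The cost is a change of timing, a sentence on the denominator, and an early IAQ for about two families at the forecast dropout (a short parent form and a short young-person form each). The downside is that the reported figure may be less favourable, and some families who leave may still decline to answer.
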